Obesity is a modifiable risk factor for several cancers, including colorectal cancer [38]. Several studies have evaluated the effects of Mindfulness on eating behavior to support weight management. Stress-induced emotional eating is often associated with the consumption of “comfort foods” that tend to be more energy dense [39]. To determine the effect of Mindfulness on eating behavior, Fulwiler et al. used the “Three-Factor Eating Questionnaire”, an assessment that measures three aspects of eating behavior: cognitive restraint, uncontrolled eating, and emotional eating, to determine if emotional eating shifted in response to a Mindfulness intervention [40]. They presented the hypothesis that high levels of emotional eating could predict weight gain, while low levels of emotional eating could predict weight loss. They found in their study that Mindfulness was associated with reduced levels of emotional eating, but they failed to assess participant weight change [40]. A systematic review and meta-analysis conducted in 2019 evaluated 10 Mindfulness interventions on weight control and found a significant weight reduction among the Mindfulness participants when compared to control groups [41]. Therefore, Mindfulness may reduce emotional eating, energy intake, and weight gain, thus reducing the risk of colorectal cancer.

This paper describes the design of a TRE and Mindfulness intervention among young adults with obesity and CPS. Participants will be randomized to 8 weeks of TRE, Mindfulness, TRE and Mindfulness, or Control. The primary outcomes are related to feasibility and acceptability. Secondary outcomes are related to body weight, body composition, perceived stress, metabolites of the hypothalamic–pituitary–adrenal axis, circulating cardiometabolic disease risk markers, gut microbiome, and colonic inflammation. We hypothesize that the study will be feasible (i.e., recruit ≥ 50% of those approached, retain ≥ 80% of the participants, participants in the intervention groups will complete ≥ 80% of the intervention content, and all groups will complete ≥ 80% of planned assessments) and acceptable (i.e., based on a standardized acceptability survey by Pflugeisen et al. [42], that will be assessed during week 4 of the intervention and after completing the intervention). 

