### 2.7. Data Analytic Plan

Data will be managed using REDCap [72] and analyzed using the statistical software SAS (version 9.4, SAS Institute, Cary, NC, USA). The data will be organized and stored on an encrypted server. Metadata will be available and stored in an electronic lab notebook, including details of what, where, when, why, and how data were collected and processed. 

We will summarize feasibility and acceptability metrics using descriptive statistics such as frequencies, percentages, means, and standard deviations. The results will include the recruitment rate among eligible individuals approached, adherence (i.e., % interaction with asynchronous sessions, % of days adherent to the TRE protocol), % retained through post-intervention, and scores on the acceptability survey. The feasibility and acceptability rates will be estimated as the number of feasibility and acceptability participants divided by the total number of approached participants, respectively. A 95% confidence interval for the feasibility and acceptability rates will be calculated assuming a binomial distribution. Fisher’s exact test will be used to test whether feasibility and acceptability rates are significantly higher than their threshold rates (50% or 80%), respectively. A chi-square test will be used to test its relationship with other categorical clinical factors, and a *t*-test will be used for its relationship with other continuous clinical factors instead. Adjusted logistic regression (binary outcomes) or generalized linear models (GLM) (continuous outcomes) will be employed in multivariate analyses to assess their relationship with each other as clinical factors. 

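### Section 2.7 tests one feasibility rate and one acceptability rate against 50% or 80% without tying either threshold to the criteria in the Introduction

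*Protocol article*

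**What the plan says.** The last paragraph of the Introduction makes these the main outcomes: "The primary outcomes are related to feasibility and acceptability". It then states the hypotheses. Feasibility has four numeric criteria:

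- recruitment and retention: "recruit ≥ 50% of those approached, retain ≥ 80% of the participants"
- intervention content: "participants in the intervention groups will complete ≥ 80% of the intervention content"
- assessments: "all groups will complete ≥ 80% of planned assessments"

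Acceptability is to be judged by a survey "that will be assessed during week 4 of the intervention and after completing the intervention". No percentage is attached to it.

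Section 2.7 (Data Analytic Plan) speaks of a feasibility rate and an acceptability rate, each calculated as "the number of feasibility and acceptability participants divided by the total number of approached participants, respectively". It plans a 95% binomial confidence interval for each, and a test of "whether feasibility and acceptability rates are significantly higher than their threshold rates (50% or 80%), respectively".

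**The concern.** The stated test does not match the stated hypothesis. Four feasibility criteria with two different thresholds become a single rate, and the wording does not settle which threshold applies to which rate. Acceptability, which has no threshold in the hypothesis, acquires one in the analysis section only if the reader supplies it.

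Sections 2.6.12 and 3 say that the results will inform a larger trial. If the threshold is settled only after the rates are known, one set of data can be reported as meeting or as missing the primary hypothesis. For acceptability, the same freedom extends to the choice between the two surveys.

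**Working it through.** **Inputs.** Thresholds of 50% and 80% (Introduction and section 2.7). 48 randomised and 40 expected to complete (section 2.6.12). The plan gives no alpha or sidedness for the threshold test, so one-sided 0.05 is assumed, with 0.025 shown in brackets. Forty acceptability respondents, equal to the planned completers, is also an assumption. The plan states no cut-off or power for this test, so it offers no figure to reproduce.

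**Method.** The exact one-sample binomial tail is used, because Fisher's exact test does not compare one proportion with a fixed value. With n participants and threshold p0, the one-sided p-value for r successes is P(X ≥ r), where X ~ Binomial(n, p0).

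**Step 1: the two readings side by side.**

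| Criterion (Introduction) | Threshold stated there | Section 2.7 read literally | Section 2.7 read loosely |
|---|---|---|---|
| Recruitment | 50% | 50% | 50% |
| Retention | 80% | 50%, inside one feasibility rate | 80% |
| Content | 80% | 50%, inside one feasibility rate | 80% |
| Assessments | 80% | 50%, inside one feasibility rate | 80% |
| Acceptability | none | 80%, survey occasion not named | must be inferred, survey occasion not named |

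**Step 2: smallest count that is significantly above each threshold.**

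| n | against 50% | against 80% | passes 50% and fails 80% (at 0.05) |
|---|---|---|---|
| 30 | 20 (21) | 28 (29) | 20 to 27 |
| 40 | 26 (27) | 37 (38) | 26 to 36 |
| 48 | 31 (32) | 44 (44) | 31 to 43 |

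The row for n = 30 covers the case where only the three intervention arms, at 10 completers each, answer the survey. For n = 40 the band is 26/40 = 65% to 36/40 = 90%. At its edges, 26/40 gives p = 0.040 against 50%, and 36/40 gives p = 0.076 against 80%.

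**Step 3: one result inside the band.** 30/40 = 75% gives p = 0.0011 against 50% and p = 0.84 against 80%.

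**Step 4: the literal reading applied to retention.** 32/48 = 66.7% gives p = 0.015 against 50%. The Introduction's 80% criterion needs 0.80 × 48 = 38.4, that is 39/48. So 32/48 would be significantly above the tested threshold while missing the stated one by seven participants.

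**Step 5: the denominator.** Section 2.7 divides both rates by everyone approached. If 96 are approached and 48 enrol, recruitment is 48/96 = 50% and exactly meets its criterion. No later rate on that denominator can then exceed 50%. With 40 completers, retention would read 40/96 = 41.7%, although 40/48 = 83.3% of those randomised were retained. Assigning thresholds alone is therefore not enough. Each criterion also needs its own denominator.

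**The case against.** The strongest reply is that the two figures in section 2.7 are exactly the two figures in the Introduction. The natural reading is 50% for recruitment and 80% for the rest, and section 2.7 lists recruitment and retention as separate results. On that reading nothing is contradicted; the sentence is only loosely worded. This stands in part. A reader might infer that 50% flatly contradicts the feasibility criteria, but it matches one of the four and conflicts with the other three only under the literal reading. The loose reading still leaves acceptability without a stated threshold.

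A reader might also count four candidate acceptability comparisons, two thresholds by two survey occasions, whichever way the sentence is read. That does not hold. The literal reading fixes acceptability at 80% and leaves two.

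It is tempting to attach a probability to picking the better of the two surveys. The documents give no survey data, cut-off or correlation, so any such figure is a scenario. Under the planned significance test it would also be small where true acceptability is below 80%: at a true 75%, one survey of 40 is significantly above 80% in about 0.5% of trials.

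The wording might be taken as a go/no-go rule for the next trial. The article states no progression rule. The rates and their confidence intervals will be reported whichever threshold is used, which limits the harm.

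Finally, the score that makes a participant count as finding the intervention acceptable, and the deciding survey, are details that an article may leave to the full protocol. Taken alone they would not be a finding. The mismatch between the article's own hypothesis and its own test is one.

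**Conclusion.** The point holds as a problem of mapping. Section 2.7 does not assign its two thresholds to the criteria in the Introduction. Read literally, it leaves three of the four feasibility criteria untested; read loosely, it leaves the acceptability threshold to inference. On both readings the deciding survey is open.

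The size depends on the assumed exact one-sided test at 0.05. With 40 respondents, results from 65% to 90% change verdict with the threshold. At 0.025 the band is 27 to 37 of 40. These counts use respondents or randomised participants as denominators, which departs from section 2.7 as written, because its denominator of all approached makes an 80% threshold unreachable for later rates at a recruitment rate of 50%.

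The plan should be corrected, but the trial is a pilot and the rates stay visible, so the consequence is moderate.

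**What to change.** In section 2.7, replace the pair of thresholds and the shared denominator with one line per criterion:

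- recruitment against 50%, among those approached
- retention against 80%, among those randomised
- assessments against 80%, among those randomised
- content against 80%, in the intervention groups
- acceptability against one named threshold (for example 80%) at the post-intervention survey, among respondents, with the week-4 survey descriptive and unable to replace it

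State the same acceptability criterion in the Introduction. For each line, also say whether the criterion is met by the observed rate or only by a rate significantly above the threshold. The Introduction implies the first and section 2.7 the second, and 32/40 (80%) satisfies the first with p = 0.59 on the second.

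The cost is wording only, provided it is done before outcome data are examined. The downside is that the acceptability claim becomes harder to meet than with a 50% threshold or the better of two surveys. If significance above 80% is kept as the rule, even a true rate of 90% would pass only about 42% of the time with 40 respondents.

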#### 2.3.4. Randomization

Participants (*n* = 48) will be randomly assigned 1:1:1:1 to the following groups: (1) TRE; (2) Mindfulness; (3) TRE and Mindfulness; or (4) Control. We will use a stratified randomization approach considering sex (female vs. male) to ensure balance across treatment arms. Randomization will occur after all aspects of the baseline data collection are completed.

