#### 2.6.12. Power and Sample Size 

This study is designed to evaluate the feasibility of the development of a larger study. The goal of the trial is to investigate and learn about data management, data collection methodologies, and how to design a larger study in the future. Forty-eight adults will be recruited, allowing for a 20% dropout rate, resulting in completed data collection on 40 individuals, which supports the calculation of confidence intervals for feasibility and effect size components. This feasibility-pilot study is not powered to detect statistically significant effects for improvement in chronic stress and body weight or the secondary/exploratory measures. The minimum detectable difference for these outcomes is 1 standard deviation based on the sample size in each of the four groups (n = 10/arm) between the baseline and post-intervention measurements that are correlated at r = 0.5, alpha = 0.05, and 80% power. We expect that there will be no change between baseline and post-intervention measurements in the control group. We did not consider power for the overall and multiple pairwise comparisons between different groups, nor will we correct for multiple comparisons because of the exploratory nature of the pilot study [67,68,69,70,71]. 

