Exploratory inferential statistics will be conducted, but no conclusions on the efficacy of the interventions will be drawn from the results. Initially, we will evaluate distributions, identify any outliers, and look for patterns of missing data. The continuous endpoints (stress, body weight, body composition, and cardiometabolic health) will be estimated among each of the groups, and the 95% confidence interval will be constructed assuming normal distribution, respectively. Then, a two-sample *t*-test will be utilized to compare each of the three intervention groups and the control group. GLM will be employed to estimate the adjusted difference in each of the continuous endpoints between the different groups. We will also investigate co-primary (body, weight, objective stress markers) and secondary outcomes (i.e., body composition, PSS, cardiometabolic measures) for between- and within-treatment differences and test for (treatment) × (time) interactions to compare the trends over time using generalized linear mixed models. We will investigate changes in microbial community diversity and composition (ASVs), tryptophan-related metabolites, and systemic and intestinal inflammation changes from baseline to post-intervention by treatment arm. The other binary endpoints will be compared between the different groups using Fisher’s exact test or chi-square test, respectively. Multivariate logistic regression will be further employed to compare these binary endpoints between the different groups, after adjusting for plausible confounders. Odds ratios and 95% confidence intervals will be calculated to evaluate the strength of any association that emerges.

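### The unadjusted t-tests of each arm against control should give way to one baseline- and sex-adjusted model, named as the main between-arm analysis

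*Protocol article*

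**What the plan says.** Section 2.7 (Data Analytic Plan) lists three between-arm analyses for the continuous endpoints (stress, body weight, body composition, cardiometabolic health):

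1. A two-sample t-test that "will be utilized to compare each of the three intervention groups and the control group". The article does not say whether it is run on post-intervention values or on change.
2. In the next sentence, "GLM will be employed to estimate the adjusted difference in each of the continuous endpoints between the different groups". The covariates are not listed.
3. Tests of treatment-by-time "interactions to compare the trends over time using generalized linear mixed models".

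No order of priority is given.

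Three other places bear on the choice. Sections 2.6 and 2.6.1 schedule measurement at baseline and post-intervention. Section 2.3.4 stratifies randomisation by sex. Section 2.6.12 plans on baseline and post-intervention "measurements that are correlated at r = 0.5, alpha = 0.05, and 80% power", with 10 completers per arm. That section also says: "We did not consider power for the overall and multiple pairwise comparisons between different groups".

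**The concern.** A two-sample t-test between arms discards information that the design has already paid for. It leaves out the stratification factor. It also uses the baseline value either not at all (post values) or with a fixed slope of 1 (change), which is efficient only when the correlation is close to 1.

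With three analyses and none in the lead, an endpoint can have three different arm differences, and the plan does not say which one to carry forward. That matters because section 2.6.12 justifies the sample partly by confidence intervals for effect-size components, and section 3 says the preliminary data will help to develop a fully powered trial. Wider intervals than necessary, or a choice among three estimates made after seeing them, weaken that use.

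**Working it through.** **Inputs.** From section 2.6.12: n = 10 completers per arm, correlation r = 0.5, alpha 0.05, power 80%. A two-sided test is my assumption; the article does not state sidedness. Variances are in units of the outcome variance, with equal SD at both time points. Detectable differences use the noncentral t distribution.

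**The plan's own figure.** Section 2.6.12 gives a minimum detectable difference of 1 SD between baseline and post-intervention.
- SD of change = √(2(1 − r)) = √(2 × 0.5) = 1.0 SD.
- A paired t-test with n = 10 then has 80.3% power at 1 SD, and the detectable difference at 80% power is 0.996 SD.

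The stated 1 SD is therefore reproduced, as a within-arm figure. It does not describe the comparison with control.

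**Relative variance of one arm-versus-control difference at r = 0.5.**
- t-test on post values: 1.00.
- t-test on change: 2(1 − r) = 1.00.
- ANCOVA on baseline, large sample: 1 − r² = 1 − 0.25 = 0.75.

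So the choice between post values and change makes no difference to the t-test at the planned correlation.

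**Small-sample cost of estimating the baseline slope.**
- Two arms of 10: inflation 1 + 1/16 = 1.0625, and 0.75 × 1.0625 = 0.80. Simulating 40,000 trials gave 0.80 against post values and 0.79 against change.
- Four arms of 10 in one model: inflation 1 + 1/34 = 1.029, and 0.75 × 1.029 = 0.77. Simulation of the four-arm model with baseline and sex, sex having no effect, agreed to within 0.01.

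The variance ratio of t-test to ANCOVA is thus 1/0.75 = 1.33 in large samples and 1/0.77 = 1.30 in the four-arm model at this size.

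**Detectable difference for one contrast, n = 10 per arm.**

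| Analysis | Error df | Detectable difference |
|---|---|---|
| Two-sample t-test | 18 | 1.32 SD |
| Two-arm ANCOVA, slope estimation allowed for | 17 | 1.19 SD |
| Four-arm ANCOVA with baseline and sex, slope estimation allowed for | 34 | 1.13 SD |

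Part of the step from 1.19 to 1.13 SD comes from pooling the residual variance and the slope over four arms. None of it is credited to sex: the article gives no sex effect, so that gain cannot be computed.

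**Other correlations (large-sample variance).**

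| r | Post values | Change, 2(1 − r) | ANCOVA, 1 − r² |
|---|---|---|---|
| 0.3 | 1.00 | 1.40 | 0.91 |
| 0.5 | 1.00 | 1.00 | 0.75 |
| 0.7 | 1.00 | 0.60 | 0.51 |
| 0.9 | 1.00 | 0.20 | 0.19 |

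In large samples ANCOVA does at least as well as either t-test at every r. At r = 0.9, which could be assumed for body weight, its advantage is large over post values and almost nil over change.

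**The mixed model.** With two time points, complete data and unconstrained baseline means, the treatment-by-time contrast equals the difference in mean change. At r = 0.5 it has relative variance 1.00 and does not recover the loss.

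**The case against.** The strongest reply is that the t-test is not the plan's only between-arm analysis. The very next sentence promises an adjusted GLM for the same endpoints. If baseline is among its covariates, that GLM already is the ANCOVA recommended here. A journal article may leave the covariate list to the full protocol or analysis plan, and section 2.6.7 names sex among the example covariates for the microbiome models, so adjustment for sex was contemplated. This stands. A reader might infer that the plan as a whole ignores baseline and sex and gives away a quarter of its precision. The article does not support that: the loss belongs to the t-test and, for complete data, to an unconstrained treatment-by-time contrast. It is not shown for the GLM.

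Second, 25% is a large-sample figure. That also stands: at 10 per arm the reduction is about 23% in a four-arm model and about 20% in a two-arm one.

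Third, these analyses are exploratory and unpowered, and section 2.7 rules out efficacy conclusions. This limits the consequence but does not remove it, since estimating effect sizes with intervals is one of the stated reasons for the sample size.

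Finally, the four arms could be read as a 2 × 2 factorial, and main effects would be more precise. That answers a different question and assumes no interaction, while section 2.8.4 presents the combination as the innovation. It is a preference and no error in the plan.

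**Conclusion.** The point holds for the t-test and for the missing order of priority. The article positively chooses an unadjusted comparison although baseline values and a stratification factor are available, and places it beside two other analyses without saying which one leads. At the planned r = 0.5 the t-test has about 1.3 times the variance of the adjusted model, and a detectable difference of 1.32 SD against about 1.13 SD for a single contrast.

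This rests on r = 0.5, equal SDs at both visits, 10 completers per arm and a two-sided 0.05 level. The effect of leaving out sex cannot be quantified from the article. The consequence is moderate: less precise and potentially competing effect estimates for planning the next trial, with the primary feasibility and acceptability outcomes unaffected.

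**What to change.** In section 2.7, delete the two-sample t-tests and state that the GLM is the main between-arm analysis of each continuous endpoint: post-intervention value on arm (four levels), baseline value of the same endpoint, and sex. Report the adjusted difference of each intervention arm from control with its 95% CI. Label the treatment-by-time mixed models as supportive. If the full protocol already puts baseline and sex in the GLM, only the deletion and the statement of priority are needed.

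Relative to a model with arm alone, the cost is two degrees of freedom (36 falls to 34 with 40 completers). No new data are needed. Factorial main effects may be added as an option, with the no-interaction caveat, but are not part of this correction.

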### 2.6. Data Collection and Measures

Data collection will occur at baseline and post-intervention. The following measures will be collected at both time points, unless stated otherwise:

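### The arm-versus-control t-tests carry no baseline term, and no stated analysis commits to adjusting for the endpoint's own baseline value; doing so would be a free gain in precision

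*Protocol article*

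**What the plan says.** Section 2.7 of the protocol article lists three between-arm analyses of the continuous endpoints, in this order:

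- A two-sample t-test "will be utilized to compare each of the three intervention groups and the control group". The sentence before it speaks of estimating the endpoints in each group. Neither sentence says whether the variable tested is the follow-up value or the change.
- "GLM will be employed to estimate the adjusted difference in each of the continuous endpoints between the different groups". No covariate is named.
- For the outcomes called co-primary and secondary, tests of treatment-by-time "interactions to compare the trends over time using generalized linear mixed models".

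Section 2.6 fixes two measurement times: "Data collection will occur at baseline and post-intervention". Section 2.3.4 places randomisation after all baseline data are collected, so the baseline values precede allocation.

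Section 2.6.12 supplies the planning figures: "The minimum detectable difference for these outcomes is 1 standard deviation based on the sample size in each of the four groups", with 10 per arm and baseline and post-intervention measurements "correlated at r = 0.5, alpha = 0.05, and 80% power". It also gives support for confidence intervals on effect size components as a reason for the sample size. It says that power for comparisons between groups was not considered.

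Section 2.7 sets the status of these analyses: "Exploratory inferential statistics will be conducted, but no conclusions on the efficacy of the interventions will be drawn from the results".

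**The concern.** With about 10 completers per arm, chance differences at baseline are not small. For two arms, the difference in baseline means has standard error sqrt(2/10) = 0.447 SD, so a gap above 0.5 SD has probability 2(1 − Φ(0.5/0.447)) = 0.26. By simulation, the chance that at least one of the three comparisons with control has such a gap is 0.54. A t-test on follow-up values carries the gap into the estimate. A change score over-corrects for it whenever the correlation is below 1. Adjusting for the baseline value by regression corrects by the right amount on average.

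All three methods are unbiased under randomisation, so what is at stake is precision. That matters here because the pilot is meant to deliver confidence intervals for effect sizes and, according to section 3, preliminary data for a fully powered trial. That later trial would also need the residual SD after baseline adjustment and the pre-post correlation.

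**Working it through.** **Inputs.** From section 2.6.12: n = 10 per arm, r = 0.5, alpha 0.05 (taken as two-sided, since the text does not say), power 80%. Equal SDs at both visits are assumed, scaled to 1. Detectable differences use the noncentral t distribution.

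**The plan's own figure.** The SD of a within-person change is sqrt(2(1 − r)) = sqrt(2 × 0.5) = 1.00. A paired t-test within one arm of 10 has 80.3% power at 1 SD and a detectable difference of 0.996 SD. The stated 1 SD is therefore reproduced, as a within-arm change. It is not an arm-versus-control figure, and section 2.6.12 does not present it as one.

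**The arm-versus-control contrast.** Its standard error is s × sqrt(2/10) = 0.447 s, where s depends on the analysis:

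- follow-up value: s = 1
- change score: s = sqrt(2(1 − r)) = 1.000 at r = 0.5
- ANCOVA on baseline: s = sqrt(1 − r²) = sqrt(0.75) = 0.866 at r = 0.5

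The 95% CI half-width is t × s × 0.447. At r = 0.5:

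| Analysis | df | t | CI half-width (SD) | Detectable difference (SD) |
|---|---|---|---|---|
| Follow-up t-test | 18 | 2.101 | 0.940 | 1.325 |
| Change-score t-test | 18 | 2.101 | 0.940 | 1.325 |
| Four arms pooled, no covariate | 36 | 2.028 | 0.907 | 1.288 |
| Two-arm ANCOVA | 17 | 2.110 | 0.817 | 1.151 |
| Four-arm ANCOVA | 35 | 2.030 | 0.786 | 1.116 |

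The covariate removes 1 − 0.75 = 25% of the residual variance, which is worth about 10/0.75 = 13 per arm. In the two-arm comparison the interval narrows by 1 − 0.817/0.940 = 13%. In the four-arm model, the step from 1.325 to 1.288 comes from pooling alone and the step from 1.288 to 1.116 from the covariate.

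The ANCOVA rows leave out the small cost of adjusting for a chance baseline gap. On average this multiplies the variance by 1 + 1/(within-arm df − 2). For two arms that is 1 + 1/16, so the half-width becomes 0.817 × 1.031 = 0.842 and the narrowing about 10%. For four arms it is 1 + 1/34, giving 0.786 × 1.015 = 0.798. The gain shrinks slightly but remains.

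**Other correlations.** The documents give only r = 0.5, so these values are assumed. Detectable differences in SD:

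| r | Follow-up t-test | Change-score t-test | Two-arm ANCOVA | Four-arm ANCOVA |
|---|---|---|---|---|
| 0.3 | 1.325 | 1.568 | 1.268 | 1.229 |
| 0.7 | 1.325 | 1.026 | 0.949 | 0.920 |
| 0.9 | 1.325 | 0.593 | 0.580 | 0.562 |
| 0.95 | 1.325 | 0.419 | 0.415 | 0.402 |

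Below r = 0.5 the change score does worse than the follow-up value alone. Near r = 0.95 it is almost as good as ANCOVA.

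**Body weight as an example** (assumed SD 15 to 20 kg and r 0.95 to 0.98, neither given in the documents). CI half-widths:

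- Follow-up t-test: 0.940 × 15 = 14 kg to 0.940 × 20 = 19 kg.
- Change score: 0.188 × 15 = 2.8 kg (r = 0.98) to 0.297 × 20 = 5.9 kg (r = 0.95).
- Four-arm ANCOVA: 0.181 × 15 = 2.7 kg to 0.283 × 20 = 5.7 kg.

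**The case against.** A reader might infer that the plan's effect estimates ignore baseline. The two sentences after the t-test do not support that. One promises adjusted differences, and the other a mixed model whose interaction term, with two visits, is the arm difference in change and so uses the baseline values. A reader might also infer that the body-weight estimate will be close to uninformative. That would hold only for a t-test on follow-up values. The text does not say that this is the variable tested, and the planned mixed model would give an interval of about 3 to 6 kg under the same assumptions.

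Three further points stand. The GLM's adjusted difference may turn out to be ANCOVA, since nothing excludes the own-baseline value as a covariate. A condensed article may properly leave the covariate list, and the choice of one main estimate among several, to the statistical analysis plan, so neither is a finding here. And these endpoints are exploratory, with feasibility and acceptability as the primary outcomes.

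The objection does not remove the efficiency point. At the plan's own r = 0.5, the mixed-model contrast is no more precise than a follow-up comparison with the same pooling, so it does not recover the loss. Where the article does give examples of covariates (section 2.6.7, for the microbiome), they are BMI, sex and age, not the outcome's own baseline. The exploratory label rules out efficacy claims, but it gives no reason to prefer wider intervals when interval estimates are part of the stated purpose.

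**Conclusion.** The point holds in a limited form. The t-tests as written have no baseline term, and no stated analysis commits to adjusting for the endpoint's own baseline value. At the plan's r = 0.5 and 10 completers per arm, the cost is a detectable difference of about 1.32 SD instead of 1.15 SD (two-arm ANCOVA) or 1.12 SD (four-arm, part of it from pooling). That corresponds to a confidence interval about 13% narrower from the covariate in the two-arm comparison. These figures assume a two-sided test, equal variances at both visits, a linear relation with baseline, and complete data on 10 per arm. At high correlations the gain over a change score is negligible, and only a follow-up t-test would be very imprecise. The choice causes no bias and affects no primary outcome. This is a free improvement for exploratory endpoints.

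**What to change.** In section 2.7, replace the two-sample t-tests by one four-arm model per continuous endpoint: the post-intervention value on arm, with the endpoint's own baseline value as covariate. A mixed model with the baseline means constrained to be equal across arms is equivalent and keeps participants who lack a follow-up value. Report adjusted differences of each intervention arm from control with 95% confidence intervals. For each endpoint, also report the residual SD and the pre-post correlation, so that the larger trial can be sized from them. For hair cortisol, which is opt-in (section 2.6.9), the model applies to those who gave samples.

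The change is to the analysis wording only. It needs no new data or visits and costs one degree of freedom per model.
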